#### Dietary intake

Differences in milk intake between intervention and control groups at 2, 3, 4, 5 and 6 months and age at introduction of solids will be compared using questionnaire data. Energy intake from 4-day diet diary data will be compared at 8 months.

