## Methods/Design

### Study design

The *Baby Milk* trial is an explanatory, parallel, individually randomised controlled trial of parents (mainly mothers) and their babies who are formula-fed. The focus of the primary outcome measurement is the baby, but the focus of the intervention is the caregiver. The intervention will commence when the baby is enrolled in the study (between 2 and 14 weeks) and be delivered up to 6 months. Babies will be followed up to age 1 year. In this explanatory trial, the intervention programme will be delivered by trained and quality-assured facilitators (research nurses). Participants in the control group will be offered the same number of contacts and standard advice about formula feeding, and weaning will be discussed.

Ethical approval has been obtained from the Cambridgeshire 4 Research Ethics Committee (Ref:10/H0305/9), and fully informed written consent will be taken from all participants.

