### Recruitment and retention

Parents and their babies who are partially or fully formula-feeding within 14 weeks of birth will be identified by research staff on a postnatal hospital ward; health professionals, including GPs, midwives and health visitors; and via a mail-out using the National Health Service (NHS) database (SystmOne). Most babies in England are delivered in the hospital and looked after by a community midwife for the first 2 weeks after discharge from hospital. Subsequently, they come under the care of a health visitor who records if they are formula-feeding in the NHS database. This database will be used to send a participant information sheet to parents in the catchment area. Research staff and midwives will identify babies within 2 weeks of birth. General Practices (GP, nurse, and other practice staff) will invite participants at the baby’s 6-week health check and immunisation clinics. Parents who return a reply slip expressing an interest in taking part or finding out more about the study will be contacted by research staff at the Medical Research Council (MRC) Epidemiology Unit to answer any questions, check eligibility criteria, and where appropriate, invite them for their baseline visit (at 2 to 14 weeks age). GPs and health visitors will be informed by letter if a baby under their care has been recruited into the study.

Maximising retention is an important issue and regular (4 to 6 weekly) contacts with participants in both groups should reduce attrition. The information sheet will emphasise the importance of follow-up irrespective of group allocation and adherence to the intervention. Participants who drop out from the intervention will be encouraged to attend for outcome measurements. For participants who withdraw from the trial, any data collected up to the withdrawal date will be retained and safely stored, but contact details will be removed.

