### Measurements

A summary of the measurements undertaken is presented in Table 1.

**Table 1 Tab1:** Study measures

Measures	Baseline	4 months	6 months	8 months	12 months
Questionnaire measures					
Baseline questionnaire^a^	I, C				
Milk feeds questionnaire	I, C	I, C	I, C		
Maternal attitudes^b^	I, C		I, C		
Temperament, sleep and eating behaviour^c^			I, C		
4-day diet diary^d^				I, C	
Health Service Utilisation			I,C		I, C
Maternal quality of life^e^	I, C		I,C		I,C
Maternal anxiety^f^	I, C		I,C		
Intervention evaluation			I		I
Anthropometry					
Parents’ height	I, C				
Parents’ weight	I, C		I, C		I, C
Baby weight	I, C	I	I, C		I, C
Baby supine length	I, C	I	I, C		I, C
Baby head circumference	I, C		I, C		I, C
Baby abdominal circumference	I, C		I, C		I, C
Baby skin fold thickness					I, C
Baby abdominal Ultrasound					I, C

*I* Intervention group; *C* Control group

^a^Baseline Questionnaire: Parents: Demography (age; education - age at completion and highest qualification; occupation; ethnicity; marital status - cohabiting/married/single); weight and height. Mother’s: lifestyle (smoking - during pregnancy, current alcohol consumption), pregnancy (duration, weight -before pregnancy and at time of delivery), delivery (normal, instrumental, or caesarean) and previous children (number, feeding-breast, formula, dependent on instructions/appetite/growth - Likert scale). Baby’s: sex, weight and length at birth and 6 weeks

^b^Maternal attitudes and feeding practices (questionnaire developed for use in this study): Mother’s attitudes; psychological measures based on Social Cognitive Theory (self-efficacy, outcome expectancy, intentions, and motivation); perception of baby’s weight. Type of feed (breast/ expressed/ formula/ mixed), feed on demand/routine/both; feed based on instructions/appetite/growth – Likert scale

Bottle feeds (type, frequency, amounts, duration, how reconstituted, advice followed, age when started), Breastfeeds (frequency, duration, and expressed milk). Other drinks and foods. Age at weaning (only at 6 months)

^c^Validated questionnaires used with permission from [name] and [name]

^d^Diet diary: developed in collaboration with MRC HNR, and used in the National Diet and Nutrition Survey of Infants and Young Children

^e^Quality of Life: EuroQol Visual Analogue Scale and Short Form 8

^f^Anxiety: Spiegelberger Short State Anxiety Inventory

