### Randomisation and consent

Only participants who attend for the baseline visit will be randomised to intervention or control groups in order to minimise the bias from selective drop out. Central telephone randomisation will be conducted based on a random number table (generated by an independent statistician) linked to the study database. We expect that important covariates (such as birth weight, sex, gestational age, family size, maternal BMI, smoking, ethnicity, educational level, age at entry into the study and whether predominantly formula-fed) will be balanced between groups due to the large sample size. Written informed consent will be obtained at baseline visit by a trained research assistant conducting measurements.

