The intervention will be delivered by trained facilitators (research nurses) from the baby’s enrolment in the trial (2 to 14 weeks old) to 6 months and will consist of three face-to-face sessions and two telephone contacts in addition to two leaflets based on SCT (Fig. 1). The face-to-face sessions will last approximately 30 to 45 min and the telephone contacts 15 to 20 min. Since social support is important, both parents will be encouraged to attend the face-to-face sessions. During the first session, the facilitator will talk parents through the ‘healthy infant growth and nutrition’ leaflet that explains the new feeding recommendations (Table 2) and the growth charts. The leaflet does not just impart knowledge about amounts of formula-feeds, hunger cues, growth charts and rapid weight gain, but also aims to encourage recommended feeding behaviours by strengthening self-efficacy and perceived benefits about following the recommendations. Demonstration of correct feed preparation (if required) and explanation of the feeding recommendations will be provided. Parents will be encouraged to make a feeding plan and provided with stickers to put on the formula milk packets. When the baby is 4-months old, parents will be invited for a second session and advice on weaning and feedback on baby’s growth will be provided. Two phone-calls - when the baby is age 2 to 3 months and 5 months - will be made to monitor progress with following recommendations and to support the parents with ongoing goal setting, action planning, self-monitoring and problem-solving. At the 6-month visit, the baby’s growth will be plotted on the WHO growth charts. Facilitators will feed back this information to parents, and they will be encouraged to monitor the growth of their babies also after the end of the intervention delivery at 6 months. Growth monitoring is important because parents are not very good at identifying obesity in their children [36], so any programme to prevent obesity must include early identification.

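### Milk intake is to be compared between arms at 2, 3, 4, 5 and 6 months from questionnaires, but Table 1 schedules that questionnaire after randomisation only at 4 and 6 months

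*Protocol article*

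**What the plan says.** All references are to the protocol article.

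- **Dietary intake** lists the comparison as "Differences in milk intake between intervention and control groups at 2, 3, 4, 5 and 6 months". The same sentence continues "age at introduction of solids will be compared using questionnaire data", so questionnaires are the stated source for milk intake as well as for solids.
- **Measurements, Table 1** has columns for baseline, 4, 6, 8 and 12 months. Its row for this instrument reads "Milk feeds questionnaire I, C I, C I, C", which places it at baseline, 4 months and 6 months in both arms. There is no column for 2, 3 or 5 months.
- **Recruitment and retention** puts the baseline visit at 2 to 14 weeks of age. **Randomisation and consent** adds: "Only participants who attend for the baseline visit will be randomised to intervention or control groups". Baseline therefore comes before allocation.
- **Intervention group** describes the telephone contacts in that arm: "Two phone-calls - when the baby is age 2 to 3 months and 5 months - will be made to monitor progress" with the feeding recommendations. They also support goal setting, planning and problem-solving.
- **Control group** describes calls every 4 to 6 weeks, used for general parenting topics, for checking how much and how often the baby feeds, and for keeping families in the study.

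**The concern.** The analysis section and the measurement schedule do not agree. Three of the five planned comparisons name a source that is not scheduled at those ages. The only scheduled questionnaire that can fall near 2 or 3 months is the baseline one, and its answers are given before allocation.

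Milk intake is a secondary outcome, but it is the behaviour that the intervention sets out to change. The sample size section assumes an achieved reduction in energy intake of 10 to 11%, and the mediation analyses concern effects on feeding behaviour. This comparison is how the trial will show whether the intended mechanism operated. If the analyst has to improvise a source for the early ages, the result could rest on pre-allocation values, or on telephone reports gathered for different purposes in the two arms.

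**Working it through.** The plan gives no figure to reproduce here. The check compares the schedules and then converts ages.

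**Step 1. Planned ages against scheduled questionnaires**

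| Planned age | Milk feeds questionnaire in Table 1 | All infants past the entry window? |
|---|---|---|
| 2 months | none | no |
| 3 months | none | no |
| 4 months | yes, both arms | yes |
| 5 months | none | yes |
| 6 months | yes, both arms | yes |

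Three of the five ages have no scheduled questionnaire.

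**Step 2. Ages against the entry window (2 to 14 weeks)**

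Weeks per month = 365.25 / 12 / 7 = 4.348.

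- 2 months = 2 × 4.348 = 8.70 weeks, inside the window.
- 3 months = 3 × 4.348 = 13.04 weeks, inside the window.
- 4 months = 4 × 4.348 = 17.39 weeks, at least 17.39 − 14 = 3.39 weeks after the latest entry.

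An infant who enters after 8.70 weeks has no post-randomisation value at 2 months. The same holds at 3 months for entry after 13.04 weeks. Entry age does not affect the 5-month comparison, where the only gap is the missing instrument.

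**Step 3. How many infants this could affect**

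The distribution of entry age is not given, so the shares below rest on assumed shapes over 2 to 14 weeks. Here c is the age in weeks.

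| Assumed entry | Formula for share entering after c | c = 8.70 (2 months) | c = 13.04 (3 months) |
|---|---|---|---|
| Uniform | (14 − c) / 12 | 0.442 | 0.080 |
| Triangular, skewed early | ((14 − c) / 12)² | 0.195 | 0.006 |
| Triangular, skewed late | 1 − ((c − 2) / 12)² | 0.689 | 0.153 |

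Under uniform entry, the planned recruitment of 650 to 700 would include about 287 to 309 infants not yet enrolled at 2 months.

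**Step 4. Can the telephone contacts fill the gap?**

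- They do not appear in Table 1 and are not described as questionnaires.
- The intervention arm has a single call for the 2-to-3-month period, so one infant cannot supply separate 2- and 3-month values.
- Their stated purposes differ: progress with the recommendations and coaching in one arm, general topics and feed monitoring in the other.
- The same four research nurses deliver both protocols (Training in intervention delivery and intervention fidelity), so the caller knows the allocation. Blinding is described for the anthropometry team and the dietary assessment team, not for callers.

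Nor does the article describe month-by-month recall of earlier intake within the 4- or 6-month questionnaire.

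**The case against.** The strongest reply is that the article condenses a fuller protocol and calls Table 1 a summary. Contacts every 4 to 6 weeks are described for both arms, standardised protocols cover every contact, and control calls explicitly ask about feed amounts. Feeding data near 2 to 3 and 5 months may therefore exist in both arms. This stands in part: the article does not show that data at those ages are impossible to obtain. It does show that the source it names is not scheduled then, and that the calls are not an equivalent substitute (step 4).

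Two stronger readings are tempting, and the article supports neither.

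- A reader might infer that the 2-month contrast would be attenuated in proportion to the share not yet enrolled. Nothing says that baseline values will be used as outcomes. An infant not yet enrolled has a missing value, not a diluted one.
- A reader might infer that restricting to infants enrolled early biases the contrast. Age at enrolment is fixed before allocation, so that subset still gives a randomised comparison. It loses precision and generality, not internal validity.

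It is also fair to say that the questionnaires are completed by parents who know what they were taught. Keeping only 4 and 6 months does not remove arm-dependent self-report. It does secure the same scheduled instrument in both arms, without relying on answers given to the person coaching the feeding. The per-protocol population is defined by session attendance, so this point does not touch it.

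**Conclusion.** The concern holds as an inconsistency between the Dietary intake section and Table 1. The 2-, 3- and 5-month comparisons cannot be carried out as written, because no milk feeds questionnaire is scheduled at those ages and baseline precedes randomisation. At 2 and 3 months, some infants will also lack any post-randomisation value. How many is unknown: about 44% and 8% under uniform entry, with ranges of about 20 to 69% and 1 to 15% under the skewed shapes tried. These shares describe missing data under assumed entry patterns. They do not measure bias, and the inconsistency does not depend on them.

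The primary outcome, the sample size and safety monitoring are unaffected. The point is still worth correcting, because milk intake is the intervention's direct target and a sound comparison is available from data already scheduled.

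**What to change.** Reconcile the Dietary intake section with Table 1 as follows.

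1. Make the formal between-arm comparison of milk intake at 4 and 6 months, from the milk feeds questionnaire, adjusted for baseline milk intake and age at enrolment. Baseline intake is already collected. Age at enrolment matters because time since entry at 4 months can range from about 3.4 weeks (17.39 − 14) to 15.4 weeks (17.39 − 2).
2. If telephone data at 2, 3 or 5 months are reported, name them as the source, label them descriptive, and include only infants already randomised at that age.
3. State that baseline questionnaire values are never used as outcomes.

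This is a change of wording and needs no new data collection. The price is that the formal early-age contrasts are given up.

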### Sample size calculation

The primary outcome is conditional infant weight gain from birth to 12 months of age (conditional on birth weight). Birth weight and weight at 6 and 12 months will be converted to standard deviation scores (SDS) adjusted for age and sex using the WHO 2006 growth standard. SDS refers to the number of standard deviations the measurement lies above (positive value) or below (negative value) the 50^th^ percentile (median value 0). Conditional weight gain is calculated as the change in weight SDS between birth to age 12 months, adjusted for birth weight SDS.

In the Avon Longitudinal Study of Parents and Children (ALSPAC), among 518 formula and mixed-fed infants, mean ± SD for conditional weight gain was 0.65 ± 0.87, and for energy intake at 4 months was 2768 ± 479 kJ/day. Based on those data, we estimated that our target 15 % (420 kJ/day) reduction in energy intake would lead to a (mean ± SE) 0.16 ± 0.04 lower gain in weight SDS between 0 to 8 months [37]. We have powered the study on a more conservative estimate of a 10 % to 11 % achieved reduction in energy intake, which corresponds to a difference in weight SDS of 0.11 to 0.12. However, the estimated effect size should be corrected for regression dilution because energy intake in ALSPAC was estimated from unweighed 1-day diet diaries. Lanigan et al. reported the within- (778 kJ) and between-infant (824 kJ) SD during the 5-day diet diaries in the 6- to 24-month-old infants, and this gives a regression dilution correction factor of 1.89 [38]. With a 10 % to 11 % lower calorie intake in the intervention group, we can expect a 0.20 to 0.21 SDS (0.11 to 0.12*1.89) difference between the two groups.

Sample sizes of 250 to 290 infants in each group will provide 80 % power at the two sided 5 % level to detect a 0.20 to 0.21 SDS difference in weight gain between the intervention and the control group. Allowing for around 15 % loss to follow-up, we aim to recruit 300 to 350 infants to each group.

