### Data analysis

All quantitative data will be double-entered by an experienced, independent data entry company with whom the MRC Epidemiology Unit has an established agreement. Statistical analysis will be performed using STATA™ statistical software. All qualitative data will be transcribed verbatim and analysed using Microsoft Excel™ or the Framework™ software.

Important baseline characteristics of participants in the two groups will be described. The main analyses will compare the intervention and control groups by ‘intention-to-treat’. A secondary ‘per protocol’ analysis will be undertaken among those completing the intervention programme based on attendance at 4/5 sessions (80 % attendance). Comparisons will adjust for age, sex, birth weight, age when formula-milk was started, and other potential confounding variables. Since effects may differ between babies who are fully formula-fed and those who are mixed fed (breast and bottle), provided there are sufficient babies in the two groups, sub-group analysis for the primary outcome will be calculated within each of the two feeding practice subgroups. In addition to the primary outcome of change in weight SDS from birth to 12 months, there are a number of secondary outcomes.

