#### Psychological mediators of infant-feeding behaviours

Differences in maternal attitudes, beliefs, intentions, self-efficacy, and outcome expectancies will be assessed between intervention and control groups. Mediation analyses will be conducted to examine to what extent any effect of the intervention on infant feeding behaviours is fully or partially explained by the above beliefs.

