#### Parents’ anthropometry

A useful halo-effect of our intervention would be if due to increased awareness, parents lost weight. At 12 months, we will compare parents’ BMI between intervention and control groups, adjusted for baseline measures.

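### Baseline milk intake and baseline attitude scores are collected in both arms but are not named as covariates, which gives up precision of an unstated, probably moderate, amount.

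*Protocol article*

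**What the plan says.** - **Collection.** Table 1 schedules the milk feeds questionnaire at baseline, 4 and 6 months, and maternal attitudes at baseline and 6 months, in both arms. Under Randomisation and consent, only families who attend the baseline visit are randomised. Under Questionnaires, the forms are completed before the visit.
- **Milk intake.** Dietary intake compares "Differences in milk intake between intervention and control groups at 2, 3, 4, 5 and 6 months" and does not mention baseline intake.
- **Attitudes.** The section on psychological mediators says: "Differences in maternal attitudes, beliefs, intentions, self-efficacy, and outcome expectancies will be assessed between intervention and control groups". The baseline score is not mentioned.
- **Covariates.** Data analysis says: "Comparisons will adjust for age, sex, birth weight, age when formula-milk was started, and other potential confounding variables". The last item is open-ended; the four named ones do not include baseline intake, baseline attitude score or feeding type.
- **Feeding type.** Randomisation and consent lists "age at entry into the study and whether predominantly formula-fed" among the important covariates and relies on sample size to balance them. In Data analysis, feeding type appears only as a subgroup factor for the primary outcome.
- **Where starting values are used.** Parents' BMI is compared "between intervention and control groups, adjusted for baseline measures". The primary outcome is conditional on birth weight SDS, and the growth outcomes are changes from birth and from baseline.

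**The concern.** Formula intake is the behaviour that the intervention is meant to change, and the sample size section derives the expected weight difference from a 10 % to 11 % fall in energy intake. If weight does not differ between arms, the intake comparison has to separate two explanations: intake did not change, or it changed and weight did not follow. The attitude scores play the same part one step earlier in the causal chain.

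A baseline measurement of the same quantity is usually among the better predictors of its follow-up value. Leaving it out puts variation that was present before randomisation into the error term and widens the interval. The trial also pools fully and mixed-fed babies, whose formula amounts are likely to differ from the start. The open clause on further covariates allows the baseline value but does not commit to it. It also selects covariates as confounders, whereas in a randomised comparison the useful criterion is whether a covariate predicts the outcome.

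**Working it through.** **Inputs from the protocol article (Sample size calculation)**
- "mean ± SD for conditional weight gain was 0.65 ± 0.87, and for energy intake at 4 months was 2768 ± 479 kJ/day". The intake figure is total energy in a pooled cohort of formula- and mixed-fed infants. It serves here only as a proxy for milk intake.
- Target fall in intake: 10 % to 11 % of 2768, which is 277 to 304 kJ/day.
- Analysable infants: 250 to 290 per arm. I use the midpoint, 270.

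**Input not in the article:** the correlation r between baseline and follow-up. I show 0.3, 0.5 and 0.7.

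**The plan's own figure.** No power is stated for milk intake or attitudes. For the primary outcome the article claims "80 % power at the two sided 5 % level to detect a 0.20 to 0.21 SDS difference" with 250 to 290 per arm. With n = 2 × [(1.96 + 0.84) × 0.87 / d]², d = 0.20 gives 298 and d = 0.21 gives 270. The upper end is close to the stated 290; the lower end is above the stated 250. This gap does not bear on the present point.

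**Step 1: gain from baseline adjustment.** Adjusting for a baseline value with correlation r multiplies the error variance by (1 − r²).
- Interval width is multiplied by √(1 − r²), and the equivalent gain in sample size is 1/(1 − r²).
- Detectable difference at 80 % power, in SD units, is (1.96 + 0.84) × √(2/270) × √(1 − r²), where √(2/270) = 0.0861.
- Power for 0.20 SD is Φ[0.20 / (0.0861 × √(1 − r²)) − 1.96].

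| r | Interval width | Equivalent n | Detectable (SD) | Detectable (kJ/day, SD 479) | Power, 0.20 SD |
|---|---|---|---|---|---|
| unadjusted | 1.00 | 1.00 | 0.241 | 115.5 | 64 % |
| 0.3 | 0.95 | 1.10 | 0.230 | 110 | 68 % |
| 0.5 | 0.87 | 1.33 | 0.209 | 100 | 77 % |
| 0.7 | 0.71 | 1.96 | 0.172 | 82 | 90 % |

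**Step 2: is the target fall in intake at risk?** The unadjusted SE is 479 × 0.0861 = 41.2 kJ/day. For 277 kJ/day, 277/41.2 = 6.72 and Φ(6.72 − 1.96) exceeds 99.9 %. For half the target (5 %, 138 kJ/day), power is 92 % unadjusted and 97 % at r = 0.5.

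**Step 3: a deliberately unfavourable assumption.** The SD of formula energy may exceed 479 because the breast milk of mixed-fed babies is not counted. Suppose 30 % are mixed-fed and take half the formula, and 479 applies within each feeding type. None of this is in the article.
- SD = √(479² + 0.3 × 0.7 × 1384²) = 795, and SE = 68.4 kJ/day.
- Mean formula energy = 2768 × (0.7 + 0.3 × 0.5) = 2353 kJ/day.
- A 10 % fall (235 kJ/day) has 93 % power unadjusted.
- A 5 % fall (118 kJ/day) has 41 % power unadjusted and 51 % at r = 0.5.

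**Step 4: how large could r be for intake?** The sample size section gives within- and between-infant SDs of 778 and 824 kJ. The implied reliability is 824²/(824² + 778²) = 0.53, or 1/1.89. If the milk questionnaire were as noisy as those one-day records (an assumption), r could not exceed about 0.53 even if true intake were stable, and the interval would narrow by at most 1 − √(1 − 0.53²), about 15 %.

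**Step 5: timing.** Baseline falls at 2 to 14 weeks of age, and 14 weeks is about 3.2 months. For later enrolments the 2- and 3-month intakes precede baseline, so baseline adjustment does not fit those comparisons.

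**The case against.** The best reply is that this is a condensed article and that covariates for secondary outcomes normally sit in the analysis plan, which is not shown. Nothing in the article says these comparisons are unadjusted. The open clause has room for the baseline value, and feeding type is already called important under Randomisation and consent. This stands in part: the omission may already be remedied elsewhere, and it is not an error in the text. The article does, however, give a covariate list for its comparisons in general, and that list is built for growth. Completing it is a fair request.

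Several stronger readings are tempting and are not supported.
- **That parents' BMI is the only outcome adjusted for its starting value.** The primary outcome and the growth outcomes also use starting values.
- **That the comparisons are much less precise than they could be.** This needs a high r, which the article does not give. A large loss can be produced by treating 2768 ± 479 kJ/day as formula intake in fully fed babies and assuming that feeding type at baseline persists. But that figure is total energy in pooled infants, and the article says nothing on persistence.
- **That chance imbalance in mixed feeding would bias the result.** Under randomisation the unadjusted interval already allows for it.
- **That the trial could not tell whether intake fell as planned.** Steps 2 and 3 show otherwise for the full target.

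**Conclusion.** The point holds as a modest gain in efficiency. Both measures have pre-randomisation values in both arms, and the article does not commit to using them. The omission costs precision and does not bias the total-effect comparison between arms. (The mediation analyses planned in the same section raise a separate question, not assessed here.)

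The size rests on the assumed r: slight at 0.3, moderate at 0.5, and large only near 0.7. For milk intake, measurement noise and a baseline age that varies by 12 weeks both argue against the top of that range. Attitude scores, and intake effects well below the target, stand to gain most. The kJ/day figures use an SD for total energy as a proxy and should be read with that limit.

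**What to change.** In Dietary intake, or in the analysis plan before any unblinded analysis, state that milk intake at the 4- and 6-month questionnaires is compared with baseline milk intake, age at baseline and fully or mixed-fed status at baseline as covariates. In the section on psychological mediators, state that 6-month attitude scores are compared with the baseline score as covariate. Say explicitly that the rule does not cover the 2- and 3-month intake comparisons.

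The cost is a change of wording and a few degrees of freedom. No new data are needed.
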